## Abstract

**Background:**

Noninvasive ventilation (NIV) is the recommended mode of ventilation used in acute respiratory failure secondary to an acute exacerbation of chronic obstructive pulmonary disease (AECOPD). Recent data has shown that high-flow nasal cannula (HFNC) treatment can be an alternative for patients with hypercapnic respiratory failure. The purpose of this study is to evaluate HFNC with sequential NIV versus NIV alone as the initial ventilatory strategy in AECOPD.

**Methods:**

This investigator-initiated, unblinded, single center, randomized controlled trial will be conducted in the emergency department, emergency intensive care unit, or respiratory intensive care unit of a tertiary-care urban teaching hospital. A total of 66 patients will be enrolled and randomized into the intervention group (HFNC with sequential NIV) or the control group (NIV group). The primary endpoint will be the mean difference in PaCO_2_ from baseline to 24 h after randomization. Secondary endpoints include the mean difference in PaCO_2_ from baseline to 6, 12, and 18 h, as well as the dyspnea score, overall discomfort score, rate of treatment failure, respiratory rate, rate of endotracheal intubation, length of hospital stay, and mortality.

**Discussion:**

Taking the advantages of both HFNC and NIV on AECOPD patients into account, we designed this clinical trial to investigate the combination of these ventilatory strategies. This trial will help us understand how HFNC with sequential NIV compares to NIV alone in treating AECOPD patients.

**Trial registration:**

ChiCTR2100054809.

## Introduction

### Background and rationale {6a}

Chronic obstructive pulmonary disease (COPD) is a common disease characterized by persistent respiratory symptoms and airflow limitation due to airway or alveolar abnormalities and is often caused by exposure to noxious particles or gasses [1]. The most severe exacerbation episodes may be associated with acute respiratory failure (ARF) deeming conventional oxygen therapy (COT) necessary, which is characterized by an acute worsening of respiratory symptoms. Patients with an AECOPD often present in ARF to the emergency department (ED), with or without carbon dioxide (CO_2_) retention and respiratory acidosis [1].

Noninvasive ventilation (NIV) is one of the most important treatments for patients with AECOPD [2]. The Global Initiative for Chronic Obstructive Lung Disease (GOLD) Criteria recommends NIV as the first and standard mode of ventilation to be used in ARF secondary to AECOPD. NIV improves gas exchange, decreases respiratory rate, improves acute respiratory acidosis [3], reduces respiratory work load, avoids endotracheal intubation and invasive mechanical ventilation, decreases hospital length of stay, and improves survival [4–7]. However, NIV may face failure under certain real-life clinical circumstances. Patients may not tolerate the ventilatory machine well because of several factors [8], such as worsening respiratory symptoms, discomfort related to the positive-pressure ventilation, claustrophobia related to the tight-fitting mask, airway secretions, or patient–ventilator interactions [9].

Recent evidence demonstrated that high-flow nasal cannula (HFNC) therapy has been playing an increasing role in patients with hypercapnic respiratory failure [8, 10–12]. HFNC delivers a heated (37 °C) and humidified (44 mg H_2_O/L) air-oxygen mixture to patients, with a stable fraction of inspired oxygen (FiO_2_). Compared to conventional oxygen therapy, HFNC FiO_2_ can range from 21 to 100% oxygen with a flow rate up to 60 L/min through a special nasal cannula. The high flow rate creates a positive end-expiratory pressure (PEEP) effect that may help to counterbalance intrinsic PEEP [13], reducing inspiratory resistance, providing adequate airflow, warm gases, and enhanced respiratory tract mucus clearance [9]. HFNC also washes out the anatomical dead space of the upper airways, facilitating carbon dioxide removal [13–15].

### Objectives {7}

Based on those potential mechanisms above, it is reasonable to use HFNC in AECOPD patients [1], but its efficacy and safety in such patients are not clear [16]. In order to unite the advantages of NIV and HFNC, we designed this trial to evaluate the effect of HFNC with sequential NIV versus NIV alone on patients with mild-to-moderate AECOPD.

## Materials and methods: participants, interventions, and outcomes

### Trial design and study setting {8&9}

This is an investigator-initiated, unblinded, single center, randomized controlled trial. This trial will be conducted in the emergency department, emergency intensive care unit, and respiratory intensive care unit of a large, urban, tertiary-care, teaching hospital. Written informed consent will be gained from all patients or their legal representatives. The flow chart of the clinical trial will be shown as (Fig. 1).

**Fig. 1 Fig1:**
[figure not shown]
Clinical trial flow chart

### Participants and eligibility criteria {10}

We will enroll adult patients of any gender who are 18 years old or older with a diagnosis of mild-to-moderate AECOPD according to the most recent GOLD criteria. Mild-to-moderate AECOPD is currently defined as an acute hypercapnic respiratory failure with an arterial pH between 7.25 and 7.35 and a PaCO_2_ ≥ 55 mmHg [4, 17, 18].

Exclusion criteria are as follows: (1) patients on home NIV; (2) those who have received HFNC or NIV prior to this study enrollment; (3) those who have unstable clinical conditions, such as the need for vasopressors to maintain blood pressure, acute coronary syndrome, life-threatening arrhythmias, cardiac or respiratory arrest requiring cardiopulmonary resuscitation or tracheal intubation; (4) those who refuse informed consent; (5) those who are agitated or have altered mental status characterized by a Richmond Agitation Sedation Scale (RASS, scores between − 5 and + 4, the higher the score is, the more agitated the patient is (unarousable, deep sedation, moderate sedation, light sedation, drowsy, alert and calm, restless, agitated, very agitated, combative)) ≥ 2 [17]; (6) those who are diagnosed with a failure in two or more than two organs; (7) those who have recent facial or neck trauma, congenital or pre-existing facial or neck deformities or nausea, vomiting, or hematemesis which may influence the proper application of HFNC or NIV; and (8) pregnancy [19].

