### Who will take informed consent? {26a}

Written informed consent will be collected from all trial participants or their authorized surrogates. A researcher from the research team, who is trained with the study protocol will confirm the patient’s willingness to participate and eligibility criteria and obtain an informed consent.

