#### Criteria for discontinuing the trial {11b}

Participants are allowed to discontinue and end their participation in the trial at any time for any reason. Each patient’s attending physician will make the decision to cease HFNC or NIV at any time when encountering emergency circumstances and/or for any urgent medical reasons if the patient shows signs of worsening respiratory failure or if they show one or more of the following conditions: respiratory pauses, with a loss of consciousness defined as GCS score less than 8/15 [17], bradycardia (heart rate < 50 beats per minute (bpm)) and tachy-arrythmia (heart rate > 150 bpm) [20], hypotension with a blood pressure < 90/60 mmHg [11], psychomotor agitation making nursing care impossible or requiring sedation [2], and respiratory or cardiopulmonary arrest. If such conditions happen to the patient, they may need to be intubated either to protect the airway or to manage tracheal secretions and given mechanical ventilation as per usual practice. Finally, the trial will end if the patient or legal representative rescinds their informed consent.

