#### Outcomes {12}

The primary endpoint is the mean difference in PaCO_2_ from baseline to 24 h after randomization. Secondary endpoints include the following: (1) the mean difference in PaCO_2_ from baseline to 6, 12, and 18 h after randomization; (2) dyspnea score at 6, 12, 18, and 24 h; (3) overall discomfort score related to the ventilatory strategy and proportion of patients showing poor tolerance to treatment at 24 h (e.g., complaining about noise, pressure, temperature, gastric distension, vomiting, or claustrophobia); (4) the proportion of patients who change treatment strategies (switch to the other ventilatory strategy or to no support); (5) rate of treatment failure, defined as the proportion of patients who had PaCO_2_ worsening or reduction < 10 mmHg from baseline, or worsening with no improvement of the dyspnea or respiratory rate > 30 breaths per minute; (6) respiratory rate; (7) rate of endotracheal intubation within 24 h; (8) length of hospital stay; and (9) all-cause mortality.

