### Data collection and measurement {18}

We will collect patient personal and baseline clinical characteristics as delineated above (e.g., age, gender, RASS, etc.). Furthermore, we will collect vital signs, systolic and diastolic pressure, heart rate, peripheral oxygen saturation, the presence of dyspnea based on the Borg dyspnea scale (score from 0 to 10 after 6 min’ walk, 0 means no dyspnea, 10 means the maximum), the arterial blood gas at inclusion, and starting time and settings for HFNC/NIV at 6, 12, 18, and 24 h. During the study intervention, patients will have continuous SpO_2_, electrocardiogram, respiratory rate, and noninvasive blood pressure monitoring. All relevant variables and endpoints will be evaluated at 6, 12, 18, and 24 h after randomization. In particular, we will record the NIV and HFNC settings as well as the proportion of patients who change treatment modality during the study period (i.e., switch to the other ventilatory strategy or to no ventilatory support). The discomfort score related to different ventilatory strategies will also be assessed at the established time points, and the proportion of patients showing poor tolerance to the treatment but who do not interrupt or withdrawal due to noise, temperature of flow, gastric distension, vomiting, or claustrophobia will be recorded. We will also record the rate of treatment failure due to a worsening PaCO_2_, a less than 10 mmHg reduction in PaCO_2_ from baseline, a worsening or lack of improvement in dyspnea, or a respiratory rate > 30 breaths per minute. Hospital length of stay and any-cause in-hospital mortality will all be collected. The main schedule of enrolment, intervention, and assessment were listed in the Table 1.

**Table 1 Tab1:** Schedule of enrolment, intervention, and assessment

Time point	Study period						
	Enrollment	Allocation	Post-allocation				
			Start	6 h	12 h	18 h	24 h
Enrollment							
Eligibility	** × **						
Informed consent	** × **						
Allocation		** × **					
Intervention							
Intervention group			** × **	** × **	** × **	** × **	** × **
Control group			** × **	** × **	** × **	** × **	** × **
Assessment							
Patient characteristics	** × **						
Vital signs	** × **		** × **	** × **	** × **	** × **	** × **
Medical history	** × **						
Laboratory results							
ABG			** × **	** × **	** × **	** × **	** × **
RASS score			** × **	** × **	** × **	** × **	** × **
Borg Dyspnea score			** × **				** × **
Discomfort score			** × **				** × **

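### Exclusion 5 names altered mental status, but its only cut (RASS ≥ 2) removes agitated patients alone; depressed consciousness down to RASS −5 passes as printed

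*Protocol article*

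**What the plan says.** In the protocol article, section Participants and eligibility criteria {10}, the fifth exclusion covers "those who are agitated or have altered mental status characterized by a Richmond Agitation Sedation Scale". The same sentence gives the range of the scale as −5 to +4, states its direction ("the higher the score is, the more agitated the patient is"), lists the level names from unarousable upwards, and closes with the only cut: "alert and calm, restless, agitated, very agitated, combative)) ≥ 2".

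Three other places bear on the point:

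- Who will take informed consent? {26a}: "Written informed consent will be collected from all trial participants or their authorized surrogates".
- Criteria for discontinuing the trial {11b}: the conditions for ceasing HFNC or NIV include "respiratory pauses, with a loss of consciousness defined as GCS score less than 8/15". This applies after entry.
- Outcomes {12}: the secondary endpoints include "dyspnea score at 6, 12, 18, and 24 h", and an overall discomfort score.

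**The concern.** The exclusion names two groups, the agitated and those with altered mental status, but sets one threshold at the agitated end of a two-ended scale. The half of the criterion that should keep out patients with depressed consciousness has no working bound.

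Three things are at stake.

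- **Safety at entry.** All participants have acute hypercapnic respiratory failure, so depressed consciousness is a foreseeable presentation. Screening staff can follow the words and exclude such a patient, or follow the number and admit.
- **Fit with the intervention.** The intervention arm receives HFNC while awake and NIV while asleep or overnight (Intervention description {11a}). The Discussion gives a reason to be careful: HFNC during sleep may worsen CO2 retention and acidosis. The schedule does not say what an unarousable patient receives in the daytime.
- **Secondary endpoints.** A patient who cannot be roused cannot rate dyspnea or discomfort.

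**Working it through.** No sample size, power or alpha figure is involved, so there is no figure of the plan to reproduce. The check applies the printed cut to the printed scale.

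**Step 1. Match the level names to the scores.** The article lists ten names in ascending order, and the range −5 to +4 has 4 − (−5) + 1 = 10 scores.

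| RASS | Level | Excluded by RASS ≥ 2? |
|---|---|---|
| +4 | combative | yes |
| +3 | very agitated | yes |
| +2 | agitated | yes |
| +1 | restless | no |
| 0 | alert and calm | no |
| −1 | drowsy | no |
| −2 | light sedation | no |
| −3 | moderate sedation | no |
| −4 | deep sedation | no |
| −5 | unarousable | no |

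**Step 2. Count.** Excluded: 3 of 10, all on the agitated side. Admitted: 10 − 3 = 7, including all 5 levels below 0.

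**Step 3. Try the other reading of the sentence.** If the RASS cut is taken to qualify only altered mental status and not agitation, the result is no better: altered mental status is then defined by a score that only agitated patients reach.

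**Step 4. Look for a consciousness limit elsewhere.**

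- Exclusions 1, 2, 4, 7 and 8 concern home NIV, earlier HFNC or NIV, refusal of consent, facial or neck problems and vomiting, and pregnancy. None bears on consciousness.
- Exclusion 3 (unstable condition) is an open list of examples. Depressed consciousness is not among them.
- Exclusion 6 (failure of two or more organs) does not define organ failure or mention consciousness.
- The inclusion range of pH 7.25 to 7.35 limits acidosis. PaCO2 has a floor of 55 mmHg and no ceiling. Neither is a limit on consciousness.
- Consent may come from a surrogate.
- The GCS condition in {11b} is tied to respiratory pauses and is a reason to stop support after enrolment, not a reason to keep a patient out.

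So 1 of the 8 exclusions names mental state, and its number covers only one direction.

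**Step 5. Effect of a minimal repair.** Adding RASS ≤ −4 excludes 2 more levels (−4 and −5), giving 3 + 2 = 5 of 10.

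**The case against.** The strongest reply is that an obtunded patient is unlikely to be enrolled in practice:

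- Every eligible patient already has respiratory failure, so under exclusion 6 one further failing organ is enough, and coma could reasonably be counted as neurological failure.
- Exclusion 3 is open-ended.
- Section {26a} has a trained researcher confirm both eligibility and the patient's own willingness, which an unarousable patient cannot express.
- HFNC is meant for waking hours, so such a patient might be placed on NIV anyway, and the attending physician may stop support or intubate at any time.
- The words of exclusion 5 still say altered mental status, and a sensible clinician would apply them.
- The population is mild-to-moderate, at one hospital, and nothing in the document shows that coma occurs in it.
- The cut is cited to a source that is not available here, so whether it was copied, shortened or chosen deliberately cannot be judged.

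Much of this stands as a limit on impact. These provisions may well catch some or most such patients, and counting scale levels says nothing about how many patients are affected. It does not remove the defect. Each safeguard relies on discretion or an undefined term, or acts only after entry, and none states a consciousness limit. Confirmation of willingness sits in the same section as permission for surrogate consent. A clinician who excludes a comatose patient under the words of exclusion 5 does so by setting aside its number. Nor is this detail that an article leaves to a fuller document: the numeric rule is printed, and it does not do what its own words say.

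**Conclusion.** The concern holds. As printed, exclusion 5 acts only on agitation and admits every level of depressed consciousness, including unarousable. The clear error is the two deepest levels, −4 and −5. Levels −2 and −3 are a clinical judgement, and drowsiness (−1) need not be excluded.

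This is a wording defect in a safety criterion that should be corrected. The document gives no frequency of obtunded patients among those screened, so no count of affected patients and no bias in the 24 h PaCO2 comparison is claimed. The sample size calculation is unaffected. The conclusion rests on reading the level names in the order printed, which the stated direction of the scale supports. A two-sided cut may have been intended, but it is not what the article states.

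**What to change.** Keep the upper cut and add a lower one to exclusion 5, for example: *agitated (RASS ≥ +2) or with depressed consciousness (RASS ≤ −4)*. A GCS floor would serve equally well. RASS −4 to −5 is the suggested minimum; the clinical team should decide whether −3 or −2 is also excluded.

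The cost is a one-sentence protocol amendment. No new measurement is needed: RASS already has to be scored to apply exclusion 5, and Data collection and measurement {18} lists it among the "baseline clinical characteristics as delineated above (e.g., age, gender, RASS, etc", with Table 1 scheduling it from the start of treatment. The downside is possibly a few fewer eligible patients.

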### Who will take informed consent? {26a}

Written informed consent will be collected from all trial participants or their authorized surrogates. A researcher from the research team, who is trained with the study protocol will confirm the patient’s willingness to participate and eligibility criteria and obtain an informed consent.

### Interventions

#### Intervention description {11a}

In the intervention group, patients will receive HFNC when they are awake in daytime and early evening hours. When they are asleep or at night between 10 pm and 6 am, these patients will change to NIV. The HFNC group will be given a flow rate of 60 L/min and a temperature of 37° C [17]. If a patient is not tolerating these settings, flow rate and temperature will be titrated to the maximum tolerated level, but with a minimum flow rate of 30 L/min.

#### Explanation for the choice of comparators {6b}

In the control group as well as during the NIV period of the intervention group, patients will receive NIV through full or nasal mask with any available ventilator in the hospital. The ventilator will be set to Pressure Support Ventilation (PSV) mode according to usual practice, including a maximal tolerated inspiratory pressure to obtain an expired tidal volume of 6–8 mL·kg^−1^ of ideal body weight and a PEEP between 3 and 5 cm H_2_O^17^.

The FiO_2_ will be set for both groups to maintain a peripheral oxygen saturation (SpO_2_) of 88–92% [4]. Besides the ventilatory support listed above, other standard therapies will be given based on current GOLD guidelines.

#### Criteria for discontinuing the trial {11b}

Participants are allowed to discontinue and end their participation in the trial at any time for any reason. Each patient’s attending physician will make the decision to cease HFNC or NIV at any time when encountering emergency circumstances and/or for any urgent medical reasons if the patient shows signs of worsening respiratory failure or if they show one or more of the following conditions: respiratory pauses, with a loss of consciousness defined as GCS score less than 8/15 [17], bradycardia (heart rate < 50 beats per minute (bpm)) and tachy-arrythmia (heart rate > 150 bpm) [20], hypotension with a blood pressure < 90/60 mmHg [11], psychomotor agitation making nursing care impossible or requiring sedation [2], and respiratory or cardiopulmonary arrest. If such conditions happen to the patient, they may need to be intubated either to protect the airway or to manage tracheal secretions and given mechanical ventilation as per usual practice. Finally, the trial will end if the patient or legal representative rescinds their informed consent.

#### Provisions for post-trial care {30}

We expect that intervention-related severe adverse events in this trial will be unlikely because the use of HFNC and NIV are both ventilatory support in patients with respiratory failure in current practice and we will upgrade to NIV or intubation if necessary. Nevertheless, we plan to provide health care and waive the fees about ventilation for participants who may encounter trial procedure-related medical situations. Post-trial care will not be provided.

#### Outcomes {12}

The primary endpoint is the mean difference in PaCO_2_ from baseline to 24 h after randomization. Secondary endpoints include the following: (1) the mean difference in PaCO_2_ from baseline to 6, 12, and 18 h after randomization; (2) dyspnea score at 6, 12, 18, and 24 h; (3) overall discomfort score related to the ventilatory strategy and proportion of patients showing poor tolerance to treatment at 24 h (e.g., complaining about noise, pressure, temperature, gastric distension, vomiting, or claustrophobia); (4) the proportion of patients who change treatment strategies (switch to the other ventilatory strategy or to no support); (5) rate of treatment failure, defined as the proportion of patients who had PaCO_2_ worsening or reduction < 10 mmHg from baseline, or worsening with no improvement of the dyspnea or respiratory rate > 30 breaths per minute; (6) respiratory rate; (7) rate of endotracheal intubation within 24 h; (8) length of hospital stay; and (9) all-cause mortality.

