#### Sample size calculation {14}

Based on previous studies [21], we set the non-inferiority cutoff at 5 mmHg. So, we assume that in the intervention group, PaCO_2_ may not elevate more than 5 mmHg after 24 h of the high-flow nasal cannula therapy with sequential noninvasive ventilation. According to previous studies, we also assume that the PaCO_2_ of intervention group is around 54 mmHg, and the control group is around 55 mmHg. Standard deviation is 9 mmHg, after 1:1 ratio randomization, and to assess non-inferiority using an *α* = 0.05, power = 0.80, and 1-side testing, 58 subjects were needed totally. Allowing for 10% loss to follow-up, we assume that we will need to recruit 70 patients. However, if loss to follow-up is greater than 10%, we aim to continue recruitment until 58 patients have a primary outcome recorded.

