### Assignment of interventions, allocation and concealment mechanisms {16}

Patients will be randomized into either an intervention group or a control group through a 1:1 ratio using a computer-generated randomization sequence via an independent investigator, who will not be involved in the trial. Allocation concealment will be maintained using sequentially numbered sealed opaque envelopes. Each envelope contains the patient’s allocation to either control or intervention group, with a unique study patient code. An independent research assistant is responsible for keeping these envelopes unopened and allocated. The baseline is defined as the time of randomization.

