### Statistical analysis {20}

The primary and secondary endpoints will be analyzed according to the intention-to-treat principle. We will use descriptive statistical methods to measure patient characteristics and baseline clinical features. For primary and secondary outcomes, continuous variables will be presented as means ± standard deviations or median interquartile ranges (IQR). Categorical variables will be expressed as counts with percentages. We will use Student’s *T* tests or Mann–Whitney *U* tests to evaluate the differences between treatments in continuous variables according to normal distribution. Categorical variables will be compared using chi-squared or Fisher’s exact tests. All data collected will be analyzed by an independent statistical expert using SPSS (SPSS 22.0). A *p*-value < 0.05 will be considered statistically significant.

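### The primary endpoint is a change in PaCO2 tested without baseline adjustment, but the sample size rests on PaCO2 levels and an unlabelled SD of 9 mmHg, so the 80% power is not secured for the planned analysis

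*Protocol article*

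**What the plan says.** - **Endpoint.** The Abstract and Outcomes {12} define the primary endpoint as a difference over time within the patient: "from baseline to 24 h after randomization. Secondary endpoints include the following".
- **Sizing.** Sample size calculation {14} assumes PaCO2 in the "intervention group is around 54 mmHg, and the control group is around 55 mmHg". It adds "Standard deviation is 9 mmHg, after 1:1 ratio randomization" and "we set the non-inferiority cutoff at 5 mmHg". With one-sided α of 0.05 and power 0.80 it arrives at 58 evaluable patients and plans to recruit 70. It gives no SD of change and no correlation between baseline and 24 h.
- **Test.** Statistical analysis {20} plans Student's t or Mann-Whitney U "tests to evaluate the differences between treatments in continuous variables according to normal distribution". It mentions no baseline covariate.
- **Baseline.** The allocation section states: "The baseline is defined as the time of randomization". Data collection and measurement {18} speaks of a blood gas at inclusion. In Table 1 the ABG row has its first mark at Start, under Post-allocation, and none at Enrollment.

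**The concern.** Endpoint, sizing inputs and test are all fixed in the article, and they are not on the same scale. The values 54 and 55 mmHg are levels. They are most naturally 24 h levels, because entry requires PaCO2 of at least 55 mmHg, so a group mean of 54 cannot be a baseline mean. A change score has a different SD from a level, and it is the larger of the two when baseline and 24 h values are weakly correlated. Power computed with the SD of a level then does not carry over to an unadjusted test of change.

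At stake is whether a non-inferiority trial with only 58 secured patients has the power it claims, and whether it leaves unused the precision that a baseline value measured in every patient would give.

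**Working it through.** **Inputs from the Sample size section.** Margin 5 mmHg; means 54 (intervention) and 55 (control), so the assumed true difference is −1 and the distance to the margin is 5 − (−1) = 6 mmHg; SD 9; one-sided α 0.05; 58 evaluable, 29 per arm.

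**Assumptions, not in the document.** SD 9 is the SD of 24 h PaCO2. The baseline SD (6, 9 or 12) and the baseline-24 h correlation ρ are varied.

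**Step 1: reproduce the plan's figure.** The normal approximation gives 2 × (1.645 + 0.842)² × 9² / 6² ≈ 27.8, so 28 per arm and 56 in total. With the noncentral t distribution, power is 0.793 at 28 per arm and 0.806 at 29, so 29 per arm and 58 in total. The stated 58 is reproduced, with 9 used directly as the SD of the analysed variable.

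**Step 2: SD of change.** SD_change = √(SD_b² + 9² − 2ρ·9·SD_b), where SD_b is the baseline SD. This is at most 9 when SD_b² ≤ 18ρ·SD_b, that is, when ρ ≥ SD_b/18. The break-even correlation is therefore 6/18 = 0.33, 9/18 = 0.50 and 12/18 = 0.67.

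**Step 3: power with baseline SD 9, 29 per arm (noncentral t).** Here SD_change = 9√(2(1 − ρ)) and the ANCOVA residual SD = 9√(1 − ρ²).

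| ρ | SD of change | Power, t-test on change | ANCOVA residual SD | Power, ANCOVA |
|---|---|---|---|---|
| 0 | 12.73 | 55% | 9.00 | 81% |
| 0.3 | 10.65 | 68% | 8.59 | 84% |
| 0.4 | 9.86 | 74% | 8.25 | 86% |
| 0.5 | 9.00 | 81% | 7.79 | 89% |
| 0.6 | 8.05 | 88% | 7.20 | 93% |
| 0.7 | 6.97 | 94% | 6.43 | 97% |

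The ANCOVA column ignores the one degree of freedom spent on the covariate, so the true values are slightly lower. For 80% power on change, the evaluable total needed (normal approximation) is 78 at ρ = 0.3, 68 at 0.4 and 56 at 0.5.

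**Step 4: other baseline SDs, t-test on change, 29 per arm.** At ρ = 0.3, power is 79%, 68% and 56% for baseline SD 6, 9 and 12. At ρ = 0.5 it is 89%, 81% and 67%.

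**Step 5: the other reading of SD 9.** If 9 is the SD of change, the t-test on change has the stated power (0.806). ANCOVA does no worse, because Var(change) = residual variance + (1 − slope)² × baseline variance, so the residual SD is again at most 9. Baseline adjustment therefore keeps about 80% or more under either reading.

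**The case against.** **Where the other side is right.**

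- The SD is not labelled. That it belongs to the 24 h level is an inference from the means beside it. If it is the SD of change, the stated power stands.
- A comparison of unadjusted change scores is valid and unbiased under randomisation. The loss is precision only.
- 58 is the secured minimum. With 10% loss from 70 recruited, 63 are evaluable, and power on change at baseline SD 9 (normal approximation) is 72% at ρ = 0.3 and 78% at ρ = 0.4, against 69% and 75% with 58. If all 70 were evaluable, it would be 76% and 82%. The gain is modest and does not remove the dependence on ρ.
- Covariate adjustment is often left to an analysis plan, which is not at hand. Here, however, the article itself names the unadjusted tests.

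**Stronger readings that a reader might infer, and why they fail.**

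- *The entry limit of 55 mmHg lowers ρ and so makes matters worse.* A floor on baseline also shrinks the baseline SD. With slope 0.4 the residual variance is 81 × (1 − 0.16) = 68.04. Cutting the baseline SD from 9 to 6 lowers ρ from 0.40 to 0.28, but SD_change falls from √(68.04 + 0.36 × 81) = 9.86 to √(68.04 + 0.36 × 36) = 9.00, and power rises from 74% to 81%.
- *Chance baseline imbalance adds a further error of about half the margin.* The standard error of a baseline difference would be 9√(2/29) ≈ 2.4 mmHg. Only the fraction (1 − slope) of it reaches a change score, and that part is already in the SD of change used above.
- *The baseline gas is drawn after allocation.* Eligibility needs pH and PaCO2, and the data collection text records a gas at inclusion, so a gas before allocation must exist. Table 1 shows at most a marking inconsistency.

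**Conclusion.** The concern holds as a mismatch of scale with a power risk attached. The endpoint is a change, the sizing inputs are levels with an unlabelled SD, and the planned test uses no baseline. If 9 mmHg is the SD of 24 h PaCO2, 80% power for change requires ρ of at least SD_b/18. With equal SDs at both times, power runs from 68% at ρ = 0.3 to 88% at ρ = 0.6.

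It would be too strong to conclude that the trial is underpowered. The document gives neither ρ nor the baseline SD, and a correlation above the break-even yields more than 80%. Nor is 0.5 a general threshold: it depends on equal SDs. What is firm is that baseline adjustment keeps power at about 80% or more under either reading of the SD. The change should be made, but the trial is not invalid without it.

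**What to change.** 1. In Statistical analysis {20}, make the primary analysis a linear model of 24 h PaCO2 on treatment with baseline PaCO2 as covariate. Compare the one-sided 95% upper confidence bound of the adjusted difference (intervention minus control) with 5 mmHg. The treatment coefficient is the same whether the outcome is entered as the 24 h value or as the change, so the endpoint definition can stay.
2. In Sample size calculation {14}, state whether SD 9 is that of the 24 h level or of the change, according to its source. The sponsor must settle this; it should not be assumed.
3. Reconcile the ABG row of Table 1 with the allocation section and the data collection text, so that baseline is the last blood gas before randomisation.

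The cost is wording only: baseline and 24 h PaCO2 are already collected, and no extra patients or measurements are needed. The change should be fixed before any outcome data are analysed, because adjustment chosen afterwards would be open to challenge.
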